#### Secondary outcomes

The secondary outcomes will be analyzed using ordinal regression models, adjusted for sex. In addition, each secondary endpoint will be dichotomized and analyzed using logistic regression. The dichotomization will be done by comparing baseline and follow-up data, either based on MCID when applicable or else by defining success as an improvement from baseline. All secondary endpoints will be analyzed at 1, 2, and 5 years of follow-up, but not until the study is closed.

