**Methods:**

This is a multicenter randomized, controlled, parallel-group non-inferiority trial. A total of 300 adult patients are allocated in a ratio of 1:1. The primary endpoint is reoperation for any reason at 5 years of follow-up. Sample size and power calculation were performed by estimating the reoperation rate after laminectomy to 3.5% and after laminectomy with fusion to 7.4% based on the data from the Swedish spine registry (Swespine) on patients with CSM. Secondary outcomes are the patient-derived Japanese Orthopaedic Association (P-mJOA) score, Neck Disability Index (NDI), European Quality of Life Five Dimensions (EQ-5D), Numeric Rating Scale (NRS) for neck and arm pain, Hospital Anxiety and Depression Scale (HADS), development of kyphosis measured as the cervical sagittal vertical axis (cSVA), and death. Clinical and radiological follow-up is performed at 3, 12, 24, and 60 months after surgery. The main inclusion criterium is 1–4 levels of CSM in the subaxial spine, C3–C7. The REDcap software will be used for safe data management. Data will be analyzed according to the modified intention to treat (mITT) population, defined as randomized patients who are still alive without having emigrated or left the study after 2 and 5 years.

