## Assignment of interventions: allocation

### Sequence generation {16a}

Participants will be allocated to either stand-alone laminectomy or laminectomy and fusion through randomization with a 1:1 ratio using the REDcap software (Research Electronic Data Capture), after informed consent and agreement to be included in the study. After inserting the patient’s personal number into REDcap, the program reports the random allocation of the patient according to the pre-constructed randomization list. The randomization is stratified for center and participant sex, i.e., using separate lists for each center and sex. The allocation sequence utilizes balanced blocks of three different sizes occurring in a random sequence. The principal investigator and study collaborators are blinded to the sequence, the block sizes, and the block sequence.

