## Data collection and management

### Plans for assessment and collection of outcomes {18a}

Participant baseline data are collected manually before the intervention and entered into the REDcap software by the study nurse. Baseline data include routine demographics, smoking habits, work status, on sick leave, duration of neck pain, attitude towards returning to work, use of analgesics, fine motor skills, and patient-reported outcome measures (PROMs) including P-mJOA, NDI, EQ-5D, NRS separately for arm and neck pain, and HADS. The surgeon records data electronically including diagnosis, 10-s grip and release test, 10-s foot-tapping test, surgical treatment, surgical levels, neurological impairment, Nurick grading [33], instability, type of implant, operation time, blood loss, and any perioperative complications. Follow-up postal questionnaires and PROMs are sent to the participants after 1, 2, and 5 years, postoperatively, according to Swespine routines [34, 35].

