The 10-s foot-tapping speed test (continuous variable) is performed with the participant sitting on a chair adjusted so that the hip and knee are flexed at 90° and the bilateral soles have contact with the floor. The participant is asked to move their toes up and down, tapping the floor as quickly as possible for 10 s with their heels firmly planted on the floor. The number of completed cycles of movement within 10 s is counted and both feet are tested separately. The test has been correlated to the JOA score, Nurick grade, 10-s grip and release test, and 30-m walking test [40].

All adverse events in both groups will be recorded. The adverse events will be graded according to severity (categorical variable): grade 1, any non-life-threatening complication treated without invasive procedures; grade 2, complications requiring invasive management such as surgical, endoscopic, and endovascular procedures; grade 3, life-threatening adverse events requiring treatment in an intensive care unit; and grade 4, death as a result of complications [41].

The C2–C7 Cobb angle, C2–C7 cSVA, C7 slope, and T1 slope (continuous variables) are all measured on images taken preoperatively and at 1, 2, and 5 years of follow-up [10, 42]. The development of ASP will be monitored. Participants who develop a progressive kyphosis/DJK of more than 40 mm cSVA [9] and/or C2–C7 Cobb < −10° and neurological deterioration/ASP/restenosis will undergo additional magnetic resonance imaging (MRI) and may be subject to supplementary posterior fusion/revision.

Direct costs include hospital stay related to the surgical procedure, implant-related costs, and pain medication usage. Indirect costs include pain medication usage after discharge, societal costs for absence from work, and worker compensation.

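### Secondary models adjust for sex but not for the collected baseline value, which costs power and lets chance baseline imbalance shift the change-from-baseline estimates

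*Protocol article*

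**What the plan says.** The protocol article, Statistical methods {20a}, Secondary outcomes, sets the main model: "The secondary outcomes will be analyzed using ordinal regression models, adjusted for sex". It continues: "In addition, each secondary endpoint will be dichotomized and analyzed using logistic regression". No covariate is named for that second analysis. The baseline value is used only to form the outcome: "The dichotomization will be done by comparing baseline and follow-up data". No section names a baseline score as a covariate in any outcome model.

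Outcomes {12} defines most secondary measures as change from baseline. The baseline values are collected:

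- Section {18a} lists "patient-reported outcome measures (PROMs) including P-mJOA, NDI, EQ-5D, NRS separately for arm and neck pain, and HADS" among the baseline data.
- The same paragraph covers the functional tests, and Nurick grading appears in the same list: "The surgeon records data electronically including diagnosis, 10-s grip and release test, 10-s foot-tapping test".
- Alignment parameters "are all measured on images taken preoperatively and at 1, 2, and 5 years of follow-up".

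Sequence generation {16a} balances two factors only: "The randomization is stratified for center and participant sex, i.e., using separate lists for each center and sex". No baseline score is balanced by design.

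**The concern.** A baseline score is usually the strongest available predictor of the same score at follow-up. Here the models condition on sex but not on the value from which each change is calculated. Some of the explainable variation therefore stays in the error, and a chance difference between arms at baseline carries through to the estimate.

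The responder analyses also depend on baseline. A patient with a baseline NRS of 2 cannot improve by 2.5 points. A patient with an NDI of 10% cannot improve by 17 points, if that threshold is read as points on the 0–100 scale. Such patients cannot respond under either treatment.

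Objectives {7} hypothesises fewer reoperations without a loss in functional scores, and the second half of that statement rests on these secondary models. Sample size {14} says that 300 was set by what the sites can recruit, so precision cannot easily be bought with more patients.

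**Working it through.** **The plan's own figures.** From Sample size {14}: 300 × (1 − 0.163 − 0.05) = 236.1, so 236 analysable, or 118 per arm. For the primary endpoint, SE = √[(0.035×0.965 + 0.074×0.926)/118] = 0.0294. Power = Φ[(0.05 + 0.039)/0.0294 − 1.96] = 85.6%, in line with the stated 86%. No power is stated for any secondary outcome, and the primary figure is not affected by this point.

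**Assumptions.** The document gives neither the baseline–follow-up correlation ρ nor an effect size for secondary outcomes. I use ρ = 0.3, 0.5 and 0.7, equal SDs at both times, and an effect of 0.365 SD. That effect is the one detectable with 80% power from the follow-up score alone: (1.96 + 0.84) × √(2/118) = 0.365.

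**Chance imbalance.** The SE of the difference in baseline means is √(2/118) = 0.130 SD, so the 95% limit is 1.96 × 0.130 = 0.255 SD. A baseline difference Δ moves a change estimate by (1 − ρ)Δ in size, and a follow-up estimate by ρΔ:

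| ρ | change | follow-up score |
|---|---|---|
| 0.3 | 0.18 SD | 0.08 SD |
| 0.5 | 0.13 SD | 0.13 SD |
| 0.7 | 0.08 SD | 0.18 SD |

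The 236 is the five-year count, and many secondary outcomes are read at 2 years. With no loss at all (150 per arm) the limit is 1.96 × √(2/150) = 0.226 SD, and the change estimate moves by 0.16, 0.11 and 0.07 SD.

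**Linear-scale reference.** In units of the outcome variance, the treatment-effect variance is 2(1 − ρ) for change and 1 − ρ² after baseline adjustment. The ratio is (1 + ρ)/2 = 0.65, 0.75, 0.85. Corresponding power at 118 per arm is 66% vs 84%, 80% vs 90% and 95% vs 98%. These ratios belong to a linear model, so the planned model type was simulated as well.

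**Proportional-odds simulation.** There were 800 trials per setting with 118 per arm. The score was integer and P-mJOA-like (0–18), with baseline mean 12.5 and SD 2.5. Sex was split 27/73 with no effect of its own. Power is the share of trials with z > 1.96:

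| ρ | change, sex | change, sex + baseline | follow-up, sex | follow-up, sex + baseline |
|---|---|---|---|---|
| 0.3 | 63% | 82% | 76% | 81% |
| 0.5 | 76% | 89% | 77% | 89% |
| 0.7 | 92% | 97% | 76% | 96% |

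Simulation error is about √(0.76×0.24/800) = 1.5 points. For the sex-only change model, the correlation of z with baseline imbalance was −0.57, −0.51 and −0.37. With baseline added it was 0.03, 0.01 and 0.05. Power is lost whether the ordinal response is the change or the follow-up score.

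**Where the gain appears.** A smaller simulation (60 trials per setting, assumed 0.3 SD effect) gave SEs of the treatment log-odds of 0.230, 0.230 and 0.232 for change with sex only. For the follow-up score with sex and baseline they were 0.232, 0.234 and 0.240. The SE does not fall. Power rises because the conditional coefficient is larger relative to its SE.

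No power figure was computed for the responder models. The point there rests on the floor arithmetic given above.

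**The case against.** The strongest case against is that one sentence in a condensed article covers many different outcomes, several without a baseline score. It says adjusted for sex without excluding other terms, and outcome-specific covariates may sit in an analysis plan that is not shown. That is fair as a caution. Still, the article states a covariate set, and that set omits the baseline value. A reader following it would fit the sex-only model.

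A reader might infer more than the document supports:

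- **Confounding by regression to the mean.** Allocation is randomised. The unadjusted comparison is unbiased over randomisations and type I error is not inflated. What remains is a conditional shift from chance imbalance.
- **Wider confidence intervals.** This is true of a linear model, not of the log-odds scale used here.
- **A fixed gain of about one third more patients.** That is the linear result at ρ = 0.5 (1/0.75 = 1.33). Over the range shown for change scores it runs from 1/0.85 = 1.18 to 1/0.65 = 1.54, and it does not translate directly to the ordinal model.
- **A threat to satisfaction or to the main conclusion.** Satisfaction is a postoperative rating with no baseline. The only non-inferiority margin is for reoperation.

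It is also true that the severity-graded P-mJOA thresholds already take some account of baseline.

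**Conclusion.** The point holds as a loss of efficiency in the secondary change-from-baseline outcomes. For a change analysis the gain from adding baseline is about 19, 13 and 5 percentage points of power at ρ = 0.3, 0.5 and 0.7. It also removes a possible shift of 0.08 to 0.18 SD at the 95% limit of chance imbalance. These sizes depend on the assumed correlations, the assumed 0.365 SD effect and 118 per arm. For change scores the gain shrinks as ρ approaches 1; for follow-up scores it grows. Validity is not at stake and the primary analysis is untouched. The change is worth making because the data are already collected.

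**What to change.** For each secondary outcome with a baseline measurement, add the baseline value of the same measure, alongside sex, to the ordinal model and to the logistic responder model. Leave satisfaction, adverse events, costs and mortality as they are. Whether centre, the other stratification factor, should also enter is a separate question.

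Costs:

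- The odds ratio becomes conditional on baseline and should be reported as such.
- Missing baseline values need a stated rule. Section {20c} provides multiple imputation for PROMs only and excludes radiographs, so baseline alignment is not covered. The surgeon-recorded tests are not PROMs either.
- Section {25} requires changes to the approved protocol to be resubmitted for ethical approval and reported, so the new wording has to be recorded as an amendment.

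Section {20a} defers the secondary analyses until the study is closed, so the change can still be prespecified if it is made before anyone sees outcomes by arm.

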Secondary outcome measures will be:Change from baseline in myelopathy score on the patient-derived modified Japanese Orthopaedic Association scale (P-mJOA) at 2 years of follow-upChange of at least 1 in mild myelopathy (>14 p), 2 in moderate myelopathy (12–14 p), and 3 in severe myelopathy (<12 p)Change from baseline in participant’s disability score on the Neck Disability Index (NDI) at 2 years of follow-upChange of at least 17% [28] in the NDI (0–100%) compared with baseline (adjustable according to results from own minimal clinically important change results for NDI)Change from baseline in myelopathy score on the Nurick scale at 2 yearsChange from baseline in the patient Quality of Life Five Dimensions (EQ-5D index) at 2 yearsChange from baseline in pain scores on the Numeric Rating Scale (NRS) at 2 yearsPain relief, as defined by ≥2.5 points [29] improvement on a 10-graded numeric rating scale for arm/shoulder painChange from baseline in the number of participants with psychological impairment on the Hospital Anxiety and Depression Scale (HADS) in both groups at 2 yearsThe cutoff for depression is defined as >10 p [30]Change in the number of satisfied participants on the satisfaction index in both groups at 2 yearsChange from baseline in myelopathy on the 10-s grip and release test at 2 yearsChange from baseline in myelopathy on the 10-s foot-tapping speed test at 2 yearsDifference in the number of participants with treatment adverse events in both groups at 5 yearsChange from baseline in sagittal alignment described as cSVA and C2–C7 Cobb angle in neutral radiographs at 5 yearsNumber of participants with a change in adjacent segment pathology (ASP) on MRIs from baseline to 5 years of follow-upNumber of participants with a change in compression of the spinal cord on the index level on MRIs from baseline to 5 years of follow-upChange in direct costs between the groups at 1 year of follow-upChange in indirect societal costs at 1 year of follow-upMortality at 5 years of follow-up

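### The blanket analysis rule for secondary outcomes also covers the two cost endpoints, where it gives an odds ratio instead of a cost difference and a baseline split that direct costs cannot support

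*Protocol article*

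**What the plan says.** Outcomes {12} introduces its list with "Secondary outcome measures will be". Two items near the end of that list are a between-group contrast in direct costs and the indirect societal costs, each at 1 year.

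Statistical methods {20a}, Secondary outcomes, sets one rule for the whole list: "The secondary outcomes will be analyzed using ordinal regression models, adjusted for sex". It continues: "In addition, each secondary endpoint will be dichotomized and analyzed using logistic regression". The split compares baseline with follow-up, "either based on MCID when applicable or else by defining success as an improvement from baseline". The same paragraph schedules every secondary endpoint for analysis at 1, 2 and 5 years.

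The costs are defined under Plans for assessment and collection of outcomes {18a}, Secondary outcomes: "Direct costs include hospital stay related to the surgical procedure, implant-related costs, and pain medication usage", and "Indirect costs include pain medication usage after discharge, societal costs for absence from work, and worker compensation". The baseline list in {18a} reads in part: "Baseline data include routine demographics, smoking habits, work status, on sick leave, duration of neck pain, attitude towards returning to work, use of analgesics". It contains no baseline cost. The article states no separate method for costs.

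**The concern.** A comparison of costs normally asks how much more, per patient, one strategy costs than the other. That is a difference in arithmetic means, and it can be multiplied up to a budget. An ordinal model reports how the odds of being in a higher cost category differ between arms. It carries no currency and gives little weight to how expensive the most expensive patients are.

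The dichotomy raises a separate problem. It needs either an MCID or a baseline value to improve on, and the main parts of direct cost have neither.

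At stake is whether two listed endpoints yield an interpretable answer. A further risk is that a skewed cost distribution makes the rank-based result and the mean difference favour different arms.

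**Working it through.** **Step 1: does the rule apply to each endpoint?** This needs only the text.

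| Element of the rule in {20a} | Direct costs | Indirect costs |
|---|---|---|
| Ordinal regression | Gives an odds ratio, not a cost difference | Same |
| Split by MCID | No cost MCID stated | No cost MCID stated |
| Split by improvement from baseline | Stay and implant costs have no preoperative value | Only partial correlates at baseline: sick leave, work status, analgesics |
| Analysis at 1, 2 and 5 years | Endpoint defined at 1 year only | Endpoint defined at 1 year only |

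**Step 2: trial size for the illustrations.** Sample size {14} starts from 300 patients, 16.3% five-year mortality and a further 5% loss: 300 × (1 − 0.163 − 0.05) = 236.1. This reproduces the stated 236, or 118 per arm. The article gives no cost figures, so every cost below is an assumption in arbitrary units.

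**Step 3: can ranks and means disagree?** Take a constructed case with 118 per arm. Every fusion patient costs 150. Of the laminectomy patients, 106 cost 100 and 12 cost 900.

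- Laminectomy mean: (106 × 100 + 12 × 900) / 118 = 21,400 / 118 = 181.4. Fusion mean: 150. Laminectomy is dearer by 31.4.
- Chance that a random laminectomy patient is cheaper than a random fusion patient: 106 / 118 = 89.8%.

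With lognormal noise added (log SD 0.25), a proportional-odds model on 20 ordered cost groups, adjusted for a simulated sex variable, gave a log odds ratio of 1.96 (SE 0.26; OR about 7.1) for fusion being costlier. In the same data laminectomy was dearer in the mean by 185.0 − 155.6 = 29.4. Disagreement is therefore possible.

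**Step 4: how often, under which assumptions?** Base costs are lognormal with medians 10 (laminectomy) and 11.5 (fusion) and log SD 0.25, and a costly event adds 40 units on average. The base means are 10 × exp(0.25²/2) = 10.32 and 11.5 × exp(0.25²/2) = 11.87. The true mean difference (laminectomy minus fusion) is 10.32 − 11.87 + 40 × (difference in event rates). The rank test is Mann-Whitney, which corresponds to the proportional-odds score test for two arms. The last column gives the share of 4,000 simulated trials in which a significant rank result (p < 0.05) opposed the sign of the sample mean difference. The first figure is for a fixed event cost, the second for an exponential one.

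| Costly-event rate, laminectomy vs fusion | True mean difference | Significant rank result opposes sample mean |
|---|---|---|
| 3.5% vs 7.4% (planning rates) | −3.1 | 0.5% to 3.1% |
| 8% vs 8% | −1.5 | 10% to 18% |
| 8% vs 0% | +1.65 | 72% to 68% |

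In the first two rows ranks and true means agree that laminectomy is cheaper. The opposition there is chance variation in a skewed sample mean.

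A second cost scale gives the same picture: base 100, fusion +20, log SD 0.25, event cost 1,000, counting any opposition in direction. At 3.5% vs 7.4% the mean difference was −59.3, with opposite directions in 1.9% of trials. With the rates swapped (7.4% vs 3.5%) it was +18.8, with opposition in 74%. So frequent reversal needs the costly tail to be concentrated in the laminectomy arm, though not necessarily confined to it. Over a wider grid with laminectomy always at the higher event rate (event cost 300–1,000, fusion surcharge 10–40), the share ran from 0.4% to 88%.

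**The case against.** The strongest reply is that the rule was written for the scored outcomes. MCIDs, baseline comparison and follow-up at 1, 2 and 5 years all fit the patient-reported scales and function tests. The rule also misfits mortality and adverse events, which suggests condensed article wording, not a considered choice of cost estimator, and health-economic methods are often set out elsewhere. Much of this is fair. It lowers the severity, and the absence of a full health-economic plan is not the complaint. It does not remove the point: the article says "each secondary endpoint will be dichotomized and analyzed using logistic regression", lists the costs as secondary outcomes, and makes no exception.

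Three stronger readings are tempting, and the documents do not support them.

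- **The trial would name the wrong arm as cheaper.** Frequent reversal needs more costly events after laminectomy. Sample size {14} plans the opposite for reoperation (3.5% vs 7.4%). Background and rationale {6a} lists infection, haematoma and dural tear as risks of both procedures and adds implant-related risks for fusion. A fusion arm with no costly tail runs against that. Whether reoperation counts as a direct cost is not stated, so even the link from reoperation to cost is an assumption.
- **An ordinal model cannot give a cost difference at all.** A mean can be derived from a fitted cumulative-probability model by a further step. The accurate statement is that the article does not include that step.
- **Costs have no baseline whatsoever.** That is clear for the stay and implant parts of direct cost. Some indirect components have correlates recorded at baseline.

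**Conclusion.** The point holds in a limited form. Two conclusions rest on the text alone. The stated analysis yields an odds ratio where the direct-cost endpoint asks for a between-group cost contrast, and the baseline split is undefined for direct costs and only partly supportable for indirect costs. The 1-, 2- and 5-year schedule also conflicts with endpoints defined at 1 year.

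The risk of a contradictory direction is secondary and conditional. It is no more than about 3% under the protocol's own planning rates, about 10–20% with equal 8% tails, and about 70% when the costly tail lies only in the laminectomy arm. These shares rest on assumed cost distributions and should not be read as forecasts. Even where directions agree, the size of the cost difference is not estimated.

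Severity is minor. Only two secondary endpoints are affected. The sample size and the primary non-inferiority conclusion are untouched, and per-participant costs can still be summarised correctly.

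**What to change.** Add an exception to Statistical methods {20a}, Secondary outcomes, for the two cost endpoints:

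- Report the difference between arms in arithmetic mean direct cost and in arithmetic mean indirect cost per participant, at 1 year only.
- Give a 95% CI from a bootstrap resampled within the randomisation strata (centre and sex), or from a generalised linear model adjusted for sex and centre with the result expressed as a difference in predicted means. If many participants have zero indirect cost, the bootstrap is simpler, because a gamma model does not accept zeros.
- Do not dichotomise costs.

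This takes one paragraph of wording and no new data. The article defers the secondary analyses until the study is closed, so the change can be recorded before any cost comparison is seen.

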Anterior and posterior decompression and fusion techniques have been compared with large sample sizes without presenting any difference in outcome [12, 13]. The question remains if fusion surgery is at all necessary as an adjunct to the decompression of the spinal cord and if CSM patients and, in that case, which CSM patients benefit from fusion surgery. After reports of postlaminectomy kyphosis in the 1970s and 1980s [14], prophylactic fusion has commonly been combined with the laminectomy procedure [12]. In a report from 1999, 34% of the patients developed kyphosis or swan neck deformity after laminectomy compared with 7% of patients surgically treated with laminoplasty, using a muscle-preserving technique [15].

A muscle-preserving technique that retains the facet integrity as well as the extensor musculature may also be used when performing posterior laminectomy. It has been observed to maintain sagittal balance after surgery without progression of kyphosis [16].

Posterior laminectomy as well as posterior laminectomy with fusion are both well-established surgical approaches. The most common surgical risks of both treatments are postoperative infection, dural tear, postoperative hematoma, neurologic deterioration, and C5 palsy. Specific risks of the muscle-preserving selective laminectomy are continuous degeneration of the affected level and progressive kyphotic deformity. Instrumented fusion may entail specific risks in terms of screw misplacement, implant failure, pseudarthrosis, increased surgical time, and blood loss [8]. Distal junction kyphosis (DJK) is a kyphotic angulation of at least 10° at the distal segment adjacent to a fused level and occurs in 24% of patients within a year after fusion surgery [17]. Adjacent segment pathology (ASP) is the progression of degeneration at the levels adjacent to a fused level and may also necessitate reoperation with laminectomy and extended fusion surgery [18].

In the lumbar spine, fusion surgery has been associated with increased operation times, blood loss, resource use, risk of complications, and 30-day mortality, when compared with laminectomy alone [19, 20]. A retrospective study in the cervical spine with a small sample size presented no differences in outcome between fusion or non-fusion groups after laminectomy, but increased operation time and blood loss in the fusion group [21].

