### Objectives {7}

The objective is to perform a non-inferiority study comparing posterior muscle-preserving selective laminectomy with laminectomy and fusion, to evaluate differences in outcome including reoperations, surgical complications, patient satisfaction, functional scores, and late degenerative changes including spondylolisthesis, kyphosis, and ASP.

We hypothesize that posterior muscle-preserving selective laminectomy is at least as successful in treating patients with CSM resulting in fewer reoperations, shorter hospital stay, and faster return to an active life, without reduced patient satisfaction, functional scores, or delayed kyphosis. Long-term follow-up radiographs and magnetic resonance imaging (MRI) are needed to assess differences in the subsequent degenerative changes including spondylolisthesis, kyphosis, and adjacent segment pathology (ASP) to compare the two strategies. Additionally, data from this study may be used to identify risk factors for the poor outcome to guide surgical decision-making.

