#### Posterior decompression and fusion

A midline incision is made over the appropriate levels, defined as the extension of laminectomy without extending beyond C3–C7 [26]. Soft tissue dissection and retraction are performed to identify osseous landmarks. Special care is taken to spare muscle attachments on C2 and C7. Spinal instrumentation is performed with lateral mass or pedicle screws (C3–C7) combined with rod fixation. Laminectomy is performed with a width not extending more than 2 mm outside the dural borders. Facet joint injury should be avoided. Special care is taken to spare the C7 spinous process and the distal half of the C7 lamina [27]. The sagittal alignment is corrected before spinal fixation. No collar or restrictions will be used [25].

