#### Imaging

Standing radiographs of the cervical spine in neutral, flexion, and extension will be performed preoperatively and at 1, 2, and 5 years of follow-up. When radiographs of the neutral position are executed, the participant will be in a comfortable standing position with the head facing forward for a horizontal gaze. The radiographs will be used to investigate the sagittal alignment by measuring the C2–C7 Cobb angle, C2–C7 cSVA, C7 slope, and T1 slope [16].

MRI of the cervical spine with T1- and T2-weighted images in sagittal and T2-weighted in axial planes will be performed preoperatively, after 3 months and at 5 years of follow-up. Hereby the compression of the spinal cord can be assessed as well as the performed decompression and the degenerative development over time.

Computed tomography (CT) will be performed pre- and postoperatively and at 3 months and 5 years to control the screw fixation, bony anatomy, and fusion (Table 2).

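### Scoring success as improvement from baseline makes the supplementary binary analyses of alignment and adjacent segment pathology unable to show worsening, and the rule does not fit endpoints without a baseline

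*Protocol article*

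**What the plan says.** All references are to the protocol article.

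- **Main secondary model** (Statistical methods {20a}, Secondary outcomes): "The secondary outcomes will be analyzed using ordinal regression models, adjusted for sex".
- **Supplementary model** (same paragraph): "In addition, each secondary endpoint will be dichotomized and analyzed using logistic regression". The cut compares baseline with follow-up and is made "either based on MCID when applicable or else by defining success as an improvement from baseline".
- **Where an MCID exists** (Plans for assessment {18a}, Secondary outcomes): values are given for P-mJOA, NDI, EQ-5D index and the pain NRS. None is given for cSVA, Cobb angle or ASP.
- **The question** (Objectives {7}): the hypothesis is that laminectomy does as well "without reduced patient satisfaction, functional scores, or delayed kyphosis". Background {6a} states: "Adjacent segment pathology (ASP) is the progression of degeneration at the levels adjacent to a fused level".
- **Endpoint list** (Outcomes {12}): alignment is a change from baseline at 5 years. ASP is a count of participants who show a change by 5 years, with no direction stated. Satisfaction, adverse events and 5-year mortality are also listed.
- **Surgery**: the fusion description includes this step: "The sagittal alignment is corrected before spinal fixation". The description of muscle-preserving laminectomy has no such step.
- **Films** (Imaging): "Standing radiographs of the cervical spine in neutral, flexion, and extension will be performed preoperatively and at 1, 2, and 5 years of follow-up".
- **A limit for worsening that is already in the document** (Outcomes {12} and {18a}): "progressive kyphosis/DJK of more than 40 mm cSVA [9] and/or C2–C7 Cobb < −10" degrees.

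**The concern.** For symptoms and function, scoring improvement as success is natural, because patients are operated on to get better. Alignment and ASP are different. The clinical worry about laminectomy alone is late kyphosis, and the worry about fusion includes degeneration at neighbouring levels. Both are forms of worsening, and a patient who stays the same has the hoped-for result. The fallback rule scores that patient as a failure, together with the patient who deteriorates.

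Responder proportions are easy to quote. A published odds ratio for alignment success could be read as an answer on delayed kyphosis when it does not measure that. The rule is also written for every secondary endpoint, and some of those have no baseline value to improve on.

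**Working it through.** **1. The plan's own figures.** Sample size {14} gives 300 randomised, 16.3% mortality, 5% other loss, and reoperation in 3.5% versus 7.4% with a margin of 5 percentage points.

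- Analysable: 300 × (1 − 0.163 − 0.05) = 236.1, against the stated 236, so 118 per arm.
- Power, normal approximation, one-sided 0.025: SE = √[(0.035 × 0.965 + 0.074 × 0.926)/118] = 0.0294, and Φ(0.089/0.0294 − 1.96) = 85.6%. Simulating the shifted permutation test, with a normal approximation to its null distribution and no sex blocking, gives 86.0%. The stated figure is 86%.

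These concern the primary endpoint only. They are used here just to fix 118 per arm.

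**2. Which endpoints the fallback governs.**

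| Endpoint | MCID in document | Baseline value | Result of the rule |
|---|---|---|---|
| P-mJOA, NDI, EQ-5D index, pain NRS | yes | yes | MCID applies |
| cSVA, Cobb angle | no | yes | stable and worse both count as failure |
| ASP | no | yes (MRI) | unchanged and progressed both count as failure |
| Adverse events, mortality | no | none | cannot be applied |
| Satisfaction | no | none: it rates the treatment result and is not among the baseline data in {18a} | cannot be applied |

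ASP is defined as progression, so few or none can improve, and the binary result says almost nothing about progression. It also does not match Outcomes {12}, which counts participants with a change.

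**3. What merging stable and worse hides.** Assume 40% improve in each arm, and 20% (laminectomy) versus 5% (fusion) worsen. These shares are illustrative and not from the document.

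- Improvement rule: 40% versus 40%, difference 0.
- Deterioration rule: 20% versus 5%. With pooled proportion 0.125, SE under the null = √(2 × 0.125 × 0.875/118) = 0.0431. SE under the alternative = √[(0.20 × 0.80 + 0.05 × 0.95)/118] = 0.0419. Power = Φ[(0.15 − 1.96 × 0.0431)/0.0419] ≈ 94%.
- With 15% versus 5%, the same formula gives about 73%.

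**4. Surgical correction in the alignment dichotomy.** The baseline film is preoperative and the next scheduled standing film is at 1 year, so correction made at operation counts as improvement. Take Cobb change as normal, so P(improved) = Φ(mean change/SD). Assume no late change in either arm and mean change 0 after laminectomy, which gives 50% improved. The fusion arm then scores:

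| SD of change | Correction 3° | 5° | 8° |
|---|---|---|---|
| 6° | 69.1% | 79.8% | 90.9% |
| 8° | 64.6% | 73.4% | 84.1% |
| 10° | 61.8% | 69.1% | 78.8% |

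The gap over 50% is 12 to 41 percentage points with no difference in late kyphosis. If the fusion arm is corrected by 5° or 8° and then loses 3° or 5°, the net means are +2° and +3°, and it still scores 58% to 69%. The SDs and corrections are assumptions. If laminectomy patients gain as much lordosis as fusion patients, the gap is zero.

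**The case against.** **The dichotomy is not the main analysis.** Ordinal regression comes first, and it registers worsening, stability and improvement alike. A reader might infer that the trial cannot detect delayed kyphosis, or that the responder analysis alone would answer that question. The document does not support this. Symptomatic kyphosis and symptomatic ASP can also reach the primary endpoint as listed reasons for reoperation. This objection stands, and it confines the point to the logistic analyses.

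**The fusion gain is real.** A reader might infer that the alignment dichotomy is biased against laminectomy, or that the gaps in step 4 are spurious. Neither follows. Correction is part of the randomised procedure, so a net gain over the preoperative film is a true effect on the endpoint as defined, and it enters any change-from-baseline analysis, including the ordinal one. The Discussion also says that lordosis may return after muscle-sparing decompression, so the net difference is unknown. What remains is a caution: such a gain is not evidence on delayed kyphosis.

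**Outcomes {12} already defines ASP, adverse events and mortality sensibly, and detailed coding can sit in a statistical analysis plan.** This is partly right, and those definitions are close to what is needed. But the analysis section states a rule for each endpoint that conflicts with them. That is a contradiction within the document, and an analysis plan that followed the rule would inherit it.

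**Isolating late loss by change from the 1-year film would mislead.** This is correct. Background {6a} puts distal junction kyphosis in 24% of patients within a year of fusion, so a 1-year starting point would absorb it.

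**Conclusion.** The point holds for the supplementary logistic analyses. For cSVA, Cobb angle and ASP, the improvement rule cannot separate stable from deteriorating patients, and so cannot show the delayed kyphosis or ASP progression that the document asks about. This follows from the wording alone and needs no distributional assumption. For mortality, adverse events and satisfaction the rule cannot be applied.

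The sizes are illustrations. Step 3 shows that a difference detectable with about 94% power can vanish completely, given the assumed shares. The 12 to 41 points in step 4 depend on assumed SDs and corrections and on no mean change after laminectomy, so they are not an estimate of bias. The primary endpoint, its margin, the sample size and the main secondary model are unaffected. The wording should be corrected, but the point does not threaten the trial's main conclusion.

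**What to change.** Amend the secondary-outcomes paragraph of Statistical methods {20a}:

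1. Restrict success as improvement to symptom and function outcomes, using the MCID where one is given.
2. Dichotomise cSVA and Cobb angle as deterioration from the preoperative film: newly exceeding the limits already in the document (cSVA > 40 mm and/or Cobb < −10°) among patients not beyond them at baseline.
3. Dichotomise ASP as new or progressed versus not, and state the same direction in Outcomes {12} so that the two sections agree.
4. Compare satisfaction, adverse events and mortality as proportions at follow-up.
5. State that improvement in alignment from the preoperative film includes surgical correction and is not evidence on delayed kyphosis. Report change from 1 to 5 years descriptively at most.

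The cost is wording. The radiographs and MRIs are already scheduled, and secondary analyses wait until the study is closed, so the definitions can be fixed beforehand. There are two small downsides. Patients beyond a limit at baseline leave the binary alignment analysis, and worsening that stays inside the limits is not counted there. Both remain covered by the ordinal analysis.
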